### Endpoints

The primary endpoint is 1-year major adverse cardiac events (MACE), defined as a combined endpoint of all-cause death, nonfatal MI, or unplanned target vessel revascularization (TVR). Secondary endpoints will include MACE at 2 and 5 years. Each individual component of the primary endpoint, cardiovascular death, target vessel-related and non-target vessel-related MI, all MI, clinically driven TVR or non-TVR, all revascularization, stent thrombosis, and angina symptom status will also be evaluated at 1-, 2-, and 5-year follow-up. All-cause death is defined as death of any cause, cardiovascular as well as noncardiovascular. MI is defined as a clinical episode of typical chest pain with development of new Q waves in at least two contiguous leads on an electrocardiogram or elevation of the creatine kinase myocardial band fraction (spontaneous, above the upper reference limit; periprocedural, more than three times the upper reference limit). Unplanned revascularization is defined as any unexpected coronary revascularization (PCI or CABG) during the follow-up period after the index procedure. TVR is defined as any repeat revascularization of any segment of the target vessel by either PCI (additional stent or angioplasty) or CABG. TVR will be considered to be ischemia-driven if revascularization is performed on a patient who has ischemic signs confirmed by noninvasive tests or FFR reassessment (with an inducible ischemia cutoff set at < 0.75), despite the presence or absence of ischemic symptoms. TVR will be considered to be clinically driven if revascularization is performed on a patient who has ischemic signs confirmed by noninvasive tests or FFR reassessment and clinical symptoms, such as chest pain that increases in frequency, intensity, or duration. Stent thrombosis is defined according to Academic Research Consortium definition [18]. Anginal status is assessed by Canadian Cardiovascular Society functional classification of angina. Clinical events are adjudicated by an independent and blinded clinical event committee.

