### Data collection and follow-up

The data will be collected using a web-based dedicated case report form. All data management and analysis will be performed centrally at the Department of Cardiovascular Medicine at the coordinating center (Wakayama Medical University, Wakayama, Japan). Members of the coordinating Center monitor and verify the data in the participating hospitals. Clinical follow-up will be performed during hospitalization; at discharge; and at 1 year, 2 years, and 5 years after allocation. The patient’s clinical status, medications, and adverse events will be evaluated and recorded during office visits or by qualified personnel via telephone contacts if office visits are impractical or impossible.

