### Statistical analysis

Continuous variables will be summarized as mean ± SD or median (IQR) for skewed data, and comparisons will be made using an unpaired Student’s *t* test or Mann-Whitney’ *U* test as appropriate. Categorical variables will be summarized as number (%), and comparisons will be made using the chi-square test or Fisher’s exact test as appropriate. Kaplan-Meier survival analysis curves will be used to assess clinical event timelines and will be compared with the log-rank test. Also, in time-to-event analyses, the treatment groups will be compared using a Cox proportional hazards model, and the results will be expressed as an HR with 95% CI. Values of *p* < 0.05 will be considered statistically significant. All statistical analyses will be conducted using JMP Pro version 14 software (SAS Institute, Cary, NC, USA).

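### Kaplan-Meier is the only method named for describing event timelines; for secondary components that death can preclude, it would slightly overstate 5-year incidence

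*Protocol article*

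**What the plan says.** The Statistical analysis section of the protocol article states that "Kaplan-Meier survival analysis curves will be used to assess clinical event timelines and will be compared with the log-rank test". It adds that "in time-to-event analyses, the treatment groups will be compared using a Cox proportional hazards model", with results given as hazard ratios and 95% confidence intervals. These are the only time-to-event methods named. For categorical data the same section says "Categorical variables will be summarized as number (%), and comparisons will be made using the chi-square test or Fisher’s exact test as appropriate". It does not say which endpoint gets which method, or how a death is treated when the endpoint is something else.

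The Endpoints section defines the primary endpoint, 1-year MACE, as "defined as a combined endpoint of all-cause death, nonfatal MI, or unplanned target vessel revascularization (TVR"). It continues: "Secondary endpoints will include MACE at 2 and 5 years". The components, cardiovascular death, several categories of MI and of revascularization, stent thrombosis and angina status "will also be evaluated at 1-, 2-, and 5-year follow-up". Under Data collection and follow-up, visits after discharge fall "at 1 year, 2 years, and 5 years after allocation".

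**The concern.** A Kaplan-Meier curve distinguishes only having had the event from not yet having had it. When the endpoint is MI or revascularization, a patient who dies first can only be censored, and the curve treats that patient as still able to have the event later. One minus Kaplan-Meier then describes a population in which nobody dies of anything else. As an estimate of the share of trial patients who have the event, it is too high. The same holds for cardiovascular death when non-cardiovascular deaths are censored.

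At stake are the 2- and 5-year incidence figures for the secondary components. If mortality differed between the arms, the overstatement would differ too, and the absolute difference read off the curves would be slightly off.

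**Working it through.** **Which endpoints are exposed.**

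- Not exposed: MACE at 1, 2 and 5 years, and all-cause death. Every death counts as an event, so nothing competes.
- Exposed to death without a prior event: the MI endpoints, target and non-target vessel revascularization, all revascularization, and stent thrombosis.
- Exposed to non-cardiovascular death only: cardiovascular death.

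**Direction.** Both estimators add up (events ÷ number at risk) over the event times, each term multiplied by a weight. In one minus Kaplan-Meier the weight is the event-free product alone, S_e. In the Aalen-Johansen estimator it is the probability of being both alive and event-free, S, which is never larger than S_e. One minus Kaplan-Meier is therefore never below the cumulative incidence, and it is above it once an event follows a competing death.

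**Size.** The article gives no mortality rate and no component rate, so there is no stated figure to reproduce on this point. The inputs below are assumptions: constant hazards, annual mortality m of 1% or 2% (5% as an upper check), and a component whose one minus Kaplan-Meier value at 5 years is 10% or 20%.

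- Event hazard: h_e = −ln(1 − c)/5, where c is the 5-year value
- Death hazard: h_d = −ln(1 − m)
- One minus Kaplan-Meier at t years: 1 − exp(−h_e·t)
- Cumulative incidence at t years: h_e/(h_e + h_d) × [1 − exp(−(h_e + h_d)·t)]

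Worked case, c = 10%, m = 1%, t = 5: h_e = 0.10536/5 = 0.02107 and h_d = 0.01005. The ratio h_e/(h_e + h_d) is 0.6771. The bracket is 1 − 0.90 × 0.99^5 = 1 − 0.8559 = 0.1441. The product is 0.0976, so cumulative incidence is 9.76% against 10%, an excess of 0.24 points.

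| 5-year 1 − KM | Annual mortality | 5-year cumulative incidence | Excess at 5 years | Excess at 2 years | Excess at 1 year |
|---|---|---|---|---|---|
| 10% | 1% | 9.76% | 0.24 | 0.04 | 0.01 |
| 10% | 2% | 9.52% | 0.48 | 0.08 | 0.02 |
| 10% | 5% | 8.84% | 1.16 | 0.20 | 0.05 |
| 20% | 1% | 19.52% | 0.48 | 0.08 | 0.02 |
| 20% | 2% | 19.06% | 0.94 | 0.17 | 0.04 |
| 20% | 5% | 17.73% | 2.27 | 0.42 | 0.11 |

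Excesses are in percentage points. For cardiovascular death, m should be non-cardiovascular mortality only, so the excess is smaller than all-cause mortality would give.

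**Against sampling error.** The binomial standard error of a 10% rate in 205 patients is √(0.10 × 0.90/205) = 2.1 points, and that of a difference between two such arms is √2 × 2.1, about 3 points. If annual mortality were 1% in one arm and 2% in the other, the distortion of the arm difference for a 10% component would be 0.48 − 0.24 = 0.24 points.

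**Sample size.** It rests on the predicted 1-year event rates alone. Diluting the deferred rate for 5% crossover gives 0.95 × 16% + 0.05 × 6.4% = 15.52%. Against 6.4%, with 80% power and two-sided 5% alpha, this needs 183 per arm by the pooled-variance formula, close to the stated 184. Then 184/0.9 rounds up to 205 per arm, as stated. Competing risks do not enter.

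**The case against.** The strongest reply is that the article never assigns Kaplan-Meier to any particular component. The sentence does not say that it covers all events, no censoring rule is given, and counts with a chi-square or Fisher test could serve for component rates at fixed times without this bias. How deaths are handled in secondary curves is also commonly left to the full protocol or the analysis plan, neither of which is shown.

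Part of this stands. That every component will be plotted by Kaplan-Meier with deaths censored is something a reader might infer, but the article does not state it, so the point has to be conditional. It is still more than missing detail. The article names one method for event timelines without restriction, and its Endpoints section uses the same term, clinical events, for the outcomes that the event committee adjudicates. The natural reading includes the components. The categorical-data sentence offers a second route for fixed-time rates but does not replace the method named for timelines.

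A reader might also infer that the log-rank test and hazard ratios for the components are invalid. They are not. With deaths censored they compare cause-specific hazards, which is a legitimate target. Only the curve and the incidence read from it are affected.

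**Conclusion.** The point holds as a minor improvement to the reporting of secondary endpoints. If Kaplan-Meier is applied to the components that death can preclude, the direction of the error is certain and its size is small: about 0.2 to 0.5 points at 5 years for a component at 10%, and 0.5 to 0.9 points at 20%. This assumes constant hazards and 1% to 2% annual mortality, neither of which comes from the article. At 1 year the excess is 0.04 points or less under the same assumptions. These amounts are below the sampling error of a single-arm rate, but they run in one direction and a larger trial would not remove them.

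A reader might arrive at larger distortions, 0.9 to 2.7 points, by letting one component run at 10% every year with mortality of 1% to 3%. That implies about 41% with that single event by 5 years (1 − 0.90^5 = 40.95%), which nothing in the article supports; its only predicted rates, 6.4% and 16%, are 1-year rates for the trial's event endpoint. Nor does the article support a reading in which the main result is biased: MACE at every time point, all-cause death and the sample size are untouched.

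**What to change.** Keep Kaplan-Meier curves for MACE and all-cause death. For every other event component, report Aalen-Johansen cumulative incidence with death as the competing event, or non-cardiovascular death when the endpoint is cardiovascular death. Keep the log-rank test and Cox model for these components and label their results as cause-specific. If a test of the incidence curves themselves is wanted, Gray's test can be added.

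This takes a sentence or two in the analysis section and a little extra programming, possibly outside the named software. It needs no new data and leaves the sample size and primary analysis as they are. The Trial status section says that recruitment had yet to open, so the change can be made before any outcome is seen.

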## Methods/design

### Study design

The Comparison of clinical outcomes following percutaneous coronary intervention versus optimal medical therapy based on gray zone fractional flow reserve in stable angina patients with intermediate coronary artery stenosis (COMFORTABLE) study is designed as a prospective, multicenter, open-label, parallel group, randomized, controlled, superiority study. This study is being conducted across 11 hospitals in Wakayama Prefecture and Tokyo, Japan. A total of 410 eligible participants will be recruited and randomized into either the performed PCI group or the deferred PCI group, with an allocation ratio of 1:1. Recruitment will begin soon.

The protocol structure was written in compliance with the Consolidated Standards of Reporting Trials (CONSORT) 2010 statement guidelines, and it follows the Standard Protocol Items: Recommendations for Interventional Trials (SPIRIT) 2013 statement. Figure 1 shows the CONSORT diagram of this study, and Fig. 2 shows the SPIRIT schedule. The complete SPIRIT checklist for the study is provided in Additional file 1.

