### Randomization

Eligible participants will be allocated to one of the two groups (medical therapy plus PCI group or medical therapy alone group) by the online randomization system. Balanced randomization based on critical variables (diabetes, age, sex, and institution) will be performed automatically by the randomization algorithm. Knowledge of the treatment allocation is open to the investigators and participants.

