### Sample size calculation

On the basis of event rates of previous studies that evaluated deferred versus performed revascularization in patients presenting coronary stenosis with gray zone FFR values, we predicted that the event rates at 1 year would be 6.4% in the revascularization group and 16% in the deferred group [15]. Under the above event rates and the hypothesis that the crossover rate from the medical therapy alone arm to the PCI arm is 5%, we calculated that a sample size of 368 patients (184 per arm) would provide the trial with 80% power to detect the superiority of medical therapy plus PCI over medical therapy by itself, at a two-sided alpha level of 5%. Assuming a dropout rate of 10% (patients lost to follow-up or patients unsuitable for analysis), the target sample size was set at 410 patients (205 per arm).

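### Randomization is balanced on diabetes, age, sex and institution, but the log-rank and Cox comparisons name none of them: a valid analysis that may give up a little power

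*Protocol article*

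**What the plan says.** Protocol article, Randomization: "Balanced randomization based on critical variables (diabetes, age, sex, and institution) will be performed automatically by the randomization algorithm". The algorithm is not named.

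Statistical analysis: "Kaplan-Meier survival analysis curves will be used to assess clinical event timelines and will be compared with the log-rank test". For time-to-event analyses it adds that "the treatment groups will be compared using a Cox proportional hazards model, and the results will be expressed as an HR with 95% CI". Neither sentence gives a stratum or covariate, and no other section carries the four factors into the analysis. Equally, no section says that the comparisons are unadjusted. The same section does fix the effect measure, the significance threshold and the software.

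Sample size calculation: the planning assumption is that "the event rates at 1 year would be 6.4% in the revascularization group and 16% in the deferred group". With 5% crossover from medical therapy alone to PCI, 368 patients (184 per arm) "would provide the trial with 80% power to detect the superiority of medical therapy plus PCI" at a two-sided 5% level. A 10% dropout allowance raises the target to 410.

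Study design: "This study is being conducted across 11 hospitals in Wakayama Prefecture and Tokyo, Japan".

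**The concern.** The article treats four baseline factors as important enough to force balance on, then describes comparisons that do not mention them. Two things follow if the factors predict MACE and the analysis ignores them.

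- The usual variance allows for chance imbalance in those factors, which the algorithm has largely removed. The test then rejects less often than its nominal 5% under the null.
- The hazard ratio is not collapsible. A Cox model that omits prognostic covariates estimates a marginal hazard ratio closer to 1 than the conditional one, and the test has somewhat less power.

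At stake is efficiency in a trial sized at 80% power on about 40 events. Validity is not at stake.

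**Working it through.** **1. The plan's own figure.** Inputs from Sample size calculation: 6.4% and 16% at 1 year, 5% crossover, two-sided 5%, 80% power.

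- Deferred rate after crossover: 0.95 × 0.16 + 0.05 × 0.064 = 0.1552. The difference is 0.1552 − 0.064 = 0.0912 and the mean rate is 0.1096.
- Two-proportion formula, pooled variance under the null, no continuity correction: n = [1.96 × √(2 × 0.1096 × 0.8904) + 0.842 × √(0.064 × 0.936 + 0.1552 × 0.8448)]² / 0.0912² = 183 per arm. The plan says 184, where power is 80.2%.
- Dropout: 184 / 0.9 = 204.4, so 205 per arm and 410 in total, as stated.

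The stated size reproduces, from a formula that uses no covariates.

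**2. Expected events.** In 368 analysed patients: 184 × (0.064 + 0.1552) = 40.3. With all 410 analysed and no dropout: 205 × 0.2192 = 44.9. The first matches the planned analysis set.

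**3. Simulated effect of leaving the factors out.** The design was 368 patients, about 40 events, and minimization on the four factors with 11 sites. The following are assumptions, not in the documents: diabetes prevalence 35%, smaller sex group 25%, age split in two for balancing, minimization probability 0.8. Prognostic strengths, also assumed:

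- *Moderate:* HR 1.5 for diabetes, 1.3 per SD of age, 1.2 for sex, sites spread over ± log 1.5.
- *Strong:* 2.5, 1.8, 1.5 and ± log 2.5.

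There were 8,000 trials per condition (four batches of 2,000) for the moderate and strong cases and 1,500 for none. Adjusted means Cox with diabetes, age and sex.

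| | Log-rank | Cox, unadjusted | Cox, adjusted | Cox, adjusted, site strata |
|---|---|---|---|---|
| Power, none | – | 81% | 81% | – |
| Power, moderate | 80.5% | 79.6% | 80.2% | 80.0% |
| Power, strong | 77.4% | 76.4% | 78.9% | 80.0% |
| Type I error, strong | 4.2% | 3.7% | 4.5% | 4.7% |

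With 8,000 trials, Monte Carlo error is about 0.5 points for power and 0.2 for type I error. All analyses were run on the same simulated trials, so the differences between columns are the result to read.

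- Strong, unadjusted Cox: loss of 78.9 − 76.4 = 2.5 points, or 80.0 − 76.4 = 3.6 with site strata. By batch, the loss was 1.8 to 3.2 points without site strata and 3.2 to 4.2 with them.
- Strong, log-rank: 78.9 − 77.4 = 1.5, or 80.0 − 77.4 = 2.6.
- Moderate: 80.2 − 79.6 = 0.6 for Cox, and no loss for the log-rank test.

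**4. A second set of assumptions.** Here diabetes prevalence was 40%, the biased coin 0.9, and site was left out of the adjusted model. There were 1,500 trials for power and 3,000 for the null.

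- Strong (diabetes 2.5, age 1.6 per SD, site SD 0.5): power 76.2% against 78.9%, type I error 3.7% against 4.9%.
- Moderate (1.8, 1.3, 0.3): power 77.5% against 78.7%, a gap of 1.2 points with Monte Carlo error of about 1 point on each figure.

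**5. Where the gain comes from.** In the strong case of step 3, under the planned effect:

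| | Mean log HR | Model SE | Ratio | 95% CI width (3.92 × SE) |
|---|---|---|---|---|
| Unadjusted | −0.91 | 0.355 | 2.56 | 1.39 |
| Adjusted | −0.945 | 0.356 | 2.65 | 1.40 |
| Adjusted, site strata | −0.98 | 0.362 | 2.71 | 1.42 |

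The interval does not shorten; the estimate moves away from zero. Under the null, the unadjusted model SE is 0.321 against a true SD of 0.314, and 0.321 / 0.314 = 1.02, an excess of about 2%. In the moderate case there is no measurable excess.

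**The case against.** The strongest objection is that the article is silent rather than wrong. A reader might infer that it commits to an unstratified log-rank test and a treatment-only Cox model; it says neither. It condenses a fuller protocol, and covariates are often specified there or in an analysis plan. That stands, and the point is worded accordingly. It does not remove the point: the section names the tests, the model, the effect measure, the threshold and the software, and carrying forward factors the trial already randomizes by would improve on that method at almost no cost.

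A reader might also infer that the planned confidence interval is materially too wide. The figures do not support this: the excess is about 2% in the strong case and unmeasurable otherwise, and the adjusted interval is no narrower.

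It is also fair to say that the marginal hazard ratio is a legitimate target, so a value closer to 1 is a different estimand and not an error. The log-rank test also loses less than the Cox model, and nothing at moderate strength. Both points stand and limit the size of the concern.

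**Conclusion.** The point holds as a minor one about efficiency. The comparisons as written do not use the balancing factors. They remain valid: in the strong case the unadjusted Cox test has a type I error of about 3.7%, below 5%.

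For the Cox comparison, the power given up is none if the factors are not prognostic, about 1 point or less if moderate, and about 2.5 to 4 points if strong. The strengths are assumptions. That the article calls the factors critical suggests its authors expect them to matter, but not by how much. It would therefore go too far to say that the test will be conservative or that power will be lost. The direction is secure if the factors are prognostic; the size is not known.

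**What to change.** Add one sentence to the analysis section. The primary comparison of 1-year MACE is a Cox model with treatment, diabetes, age (continuous) and sex as covariates, stratified by institution, with small sites pooled by a rule set before outcomes are examined. The unadjusted log-rank test and Kaplan-Meier curves are supportive. If a fuller document already says this, a cross-reference is enough.

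The variables are known at randomization, so no new data are needed. The article says recruitment has yet to open, so the choice can be fixed before any outcome exists. That also rules out a later choice between adjusted and unadjusted results in an open-label trial.

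There are two costs. The reported hazard ratio becomes conditional rather than marginal and should be labelled so. And about 40 events over four parameters is about 10 per parameter before any site term, while 40.3 / 11 is about 3.7 events per hospital, which is why small sites must be pooled.

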## Discussion

Even in the current DES era, revascularization for coronary stenosis with FFR between 0.75 and 0.80 is a matter of debate. Some studies, including our retrospective studies [12, 17], have reported that PCI compared with medical therapy alone is associated with better clinical outcomes in patients with gray zone FFR values [9, 11, 14, 15]. Conversely, other studies have shown that deferred revascularization could be the preferred initial treatment strategy for coronary stenosis with gray zone FFR values [10, 13, 16]. Thus, revascularization versus deferral decision-making for coronary stenosis presenting with gray zone FFR is controversial. However, currently available evidence is limited to registries, retrospective analyses, and single-center experiences. For FFR values between 0.75 and 0.80, the clinical decision for PCI or medical therapy has been left entirely to the operator’s discretion.

The COMFORTABLE prospective study will be the first prospective, multicenter, randomized, controlled study to prove the superiority of medical therapy plus PCI over medical therapy alone in reducing major cardiovascular events in patients presenting with coronary stenosis with gray zone FFR values. The results of the COMFORTABLE prospective study will help interventional cardiologists guide revascularization decisions for coronary stenosis with gray zone FFR values.

This study has several limitations, the most important being its open-label nature. We cannot entirely exclude the possibility that the treatment strategy will be modified, because the arm of treatment to which the patient has been allocated will be known. Second, an FFR value is limited by its reliance on the achievement of maximal hyperemia. Failure to achieve peak hyperemia, by not achieving maximal reduction in microvascular resistance, may result in overestimation of FFR and lead to wrong decision-making, especially in coronary stenosis with an FFR value in and around the “gray zone” [11]. For these reasons, in this study, we will use intravenous ATP administration to induce steady-state maximal hyperemia, and additional IC papaverine, nicorandil, or ATP should be administered if maximal hyperemia is suspicious.

